**Fig. 1 Fig1:**
[figure not shown]
Participant trajectory

For all measurement points, the assessing research assistants are blind to the participant’s research condition. The design of this study was approved by the Medical Research Ethics Committee (MREC) of the Erasmus Medical Centre in Rotterdam, number MEC-2020-0583.

### Participants

All participants (*N* = 159) will be recruited from outpatient clinics of the Parnassia Psychiatric Institute and GGZ Delfland, two institutions for mental health care in the Netherlands. To be eligible to participate in this study, a subject must be (1) at least eighteen years of age and (2) classified with any PD with the aid of the Structured Clinical Interview for DSM-5 Personality Disorders (SCID-5-P). To ensure that patients can competently decide to participate and answer the questions during the clinical interviews or the self-report questionnaires, patients will be excluded if their competency in the Dutch language is inadequate or if their IQ is estimated as lower than 70 (mental disability). The aim is to include a broad range of patients with PDs, because this represents the population that is treated within outpatient specialized mental health care centres for PDs the best.

### Recruitment

Participants who are not yet in treatment will be recruited in three ways. Firstly, in the waiting rooms of the mental health institutions that participate in this study, posters will be placed that briefly explain the goal, design and trajectory of the study. Patients can announce themselves to their therapist or contact the researchers directly. Secondly, patients with a PD will also be informed about the study by their therapist. Thirdly, researchers can directly contact patients who have given approval to being approached for research. If the patient is interested, the therapist informs the researchers, who will send them information via e-mail and invite them for an appointment with one of the researchers. Patients will receive further information about the study during the appointment and will be asked to sign an informed consent form. If consent has been given, the researcher will check eligibility for inclusion by conducting the SCID-5-P. Next, another appointment will be scheduled for baseline measurements.

Participants will receive a financial incentive of 25 euros per complete measurement, potentially totalling 125 euros for all five measurements. They receive this fee at the end of participation (i.e. completion or termination).

### Randomization

Prior to study initiation, a randomization table with 159 rows (participants) and one column (condition: 0 vs. 1; EMDR vs. waiting list; 1:1 ratio without blocks) is generated in Data Manager, an external service for administering questionnaires and safely storing responses, available at Parnassia Psychiatric Institute. Thusly, the condition of any participant is determined beforehand. After a participant has completed the baseline measurements, a case report form (CRF) is manually generated in Data Manager. The non-blind researcher can reveal the participant’s condition by pressing a randomize-button. Participants will be informed of their allocation through telephone or video calls. In Data Manager, it is pre-programmed that conditions are visible for only the non-blind researchers. In addition, the principal investigator (KS) has insight into conditions of all participants. Therefore, unblinding will never be necessary.

### Sample size calculation

In order to test the effectiveness of EMDR in reducing the number of PD symptoms over time, relative to waiting list, a linear mixed model (LMM) with intention-to-treat will be used. A RCT of five EMDR sessions revealed an effect size of .65 for change in psychological symptoms, .62 for psychological functioning and .56 for change in personality functioning [33]. Since change in personality functioning is also (primarily) assessed in the current study, although with the aid of a different measure (Assessment of DSM IV Personality disorders; ADP-IV), the effect size for the main analysis is expected to approximate the effect size found by Hafkemeijer et al. [33]. With the aid of standardization by post score standard deviations (standard procedure for meta-analyses), this effect size decreases to .46. Therefore, an effect size of .43 was estimated to be appropriate for this study. Using Liu and Liang’s [45] equation, assuming a correlation of .7 between five repeated measurements, a treatment effect size of .43, a power of .8, an *α* significance level of .05, and two treatment conditions, the power analysis resulted in a total sample size of 132 patients. With an estimated dropout rate of 20%, a total of 159 patients is needed.

### Conditions

#### EMDR therapy

Half of the participants will receive EMDR therapy. This is a standardized, eight-phase, trauma-focused therapy. The EMDR standard protocol incorporates several predetermined steps, consisting of standard questions and formulations intended as process instructions. Further, EMDR therapy consists of dosed attention directed at the disturbing memory, at the same time engaging in another concurrent (dual-attention) task [24, 55]. The task typically requires patients to follow the horizontally moving fingers of the therapist with their eyes, but taps, tones and other tasks that tax patients’ working memory [4] can also be applied. For a full description of the treatment protocol, see Shapiro [55].

In the current study, a total of ten biweekly sessions of EMDR therapy will be applied with a duration of 90 min per session. Before onset, a case conceptualization is made to guide the treatment sessions. If patients report having been exposed to traumatic events (i.e. criterion A of PTSD [1]), the EMDR sessions will target the associated traum atic memories first (intrusive before non-intrusive). If there is no clear trauma, the EMDR therapy sessions will target the memories that gave rise to or worsened the patient’s most distressing symptoms. All memories will be placed in a hierarchy based the subjective units of disturbance (SUD) and will be treated from high to low SUD. Each case conceptualization will be review ed by a highly experienced and qualified supervisor prior to the beginning of therapy. During the sessions, the Dutch version of the standard EMDR protocol [23] will be used. Participants are asked to focus on the currently most distressing memory, includin g images, thoughts, emotions and physical sensations. Besides eye movements, other forms of working memory taxation, such as hand taps or tones, are used to process the memories. 

Protocol adherence and treatment quality are improved in a number of ways. First, EMDR therapy will be provided by psychologists, psychiatrists and residents in psychiatry who have attended at least the official Dutch Basic EMDR training and in this way are certified according to the guidelines of the EMDR Europe association (EMDREA). Secondly, in advance of study initiation, all therapists need to attend an additional one-day training aimed at case conceptualization and to improve their skills needed to treat patient s suffering from a PD, provided by an EMDREA accredited trainer ([name]). Thirdly, monthly group consultations will be organized by EMDREA approved consultants. Fourthly, these consultants review the EMDR sessions through session reports that the therapists share with the consultants directly following each session. Additional consultation is available on request. Fifthly, all treatment sessions will be videotaped and coded. Therapists are obligated to show parts of their recordings during the monthly consultation sessions, so that therapists’ skills can be further improved. Lastly, 10% of all recordings will be selected (using www.randomization.com) and rated for therapist competence and treatment protocol adherence by trained and blinded assessors (EMDREA approved consultants) after conclusion of the trial.

A participant will be considered an early completer of EMDR therapy when the subjective levels of disturbance associated with the memories that were part of the case conceptualization have decreased to zero before the ten sessions have been completed, and the participant no longer meets the diagnostic criteria for a PD according to the ADP-IV. At this point, therapy is terminated. However, post-intervention data will still be collected at approximately the same moment as non-early completers. It is expected that a large proportion of the participants are able to process multiple memories per session during the ten protocolled therapy sessions. This may lead to some of the patients being considered “early completers”. In some cases, it may be decided to (temporarily) discontinue therapy, for which the following criteria apply: (1) participant request, (2) decision by primary caretaker, (3) decision by the supervising EMDR consultants or (4) admission to crisis mental health care.

After 3-month follow-up (T3), the therapist who did the diagnostic procedure on admission and the participant will confer about the current state of the participant, whether further treatment as usual for the PD is necessary and, if so, which treatment is most suitable. These treatments might be emotion regulation training and psychotherapy for PD, including schema- or dialectical behaviour therapy. However, any PD treatment is postponed until after T3.

#### Waiting list

The other half of the participants will be allocated to the control condition, namely a waiting list. They will not receive EMDR therapy and any other treatment for their PD is postponed until after T3 as well. They will be informed of their condition right away and invited for another appointment for post-intervention measurements (T1). Three months later, besides T3 assessments, all participants will confer with the therapist who did the diagnostic procedure on admission, to decide which treatment is most suitable. Patients will be offered the opportunity of following any available treatment, but not EMDR therapy, for their PD. The patient will be registered for the chosen treatment based on the date of intake so that the patient does not have additional waiting time. At study termination (T12), participants in the control condition will also be offered EMDR therapy.

### Adverse events

All adverse events reported spontaneously by the subject or observed by the investigator or his staff will be recorded. The investigator will report all serious adverse events (SAEs) to the sponsor without undue delay after obtaining knowledge of the events. The sponsor will report the SAEs through the web portal *ToetsingOnline* to the accredited medical ethical review board that approved the protocol, within 7 days of first knowledge for SAEs that result in death or are life threatening followed by a period with a maximum of 8 days to complete the initial preliminary report. All other SAEs will be reported within a period of maximum 15 days after the sponsor has first knowledge of the serious adverse events.

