Committees	Data will be processed in a data management system (Research manager), which facilitates monitoring. Via this system an Audit-trial will be created and a monitor will be assigned. Independently from the researchers and sponsor, this person will monitor the study via the research manager data management system. Furthermore, the monitor will visit the site with a minimum frequency of one visit per year. After the study, a close-out visit will be planned. The monitor will check whether study procedures are followed correctly, and will check the study site's documentation, the participants' source data, electronic Case Report Form (eCRF) entries, and the correct maintenance of the Investigator Site File. At the site, monthly research meetings take place. In these meetings, the project will be discussed with the steering committee. Furthermore, the sponsor will submit progress and safety reports to the Medical Research Ethics Committee (MREC) once a year, informing them of the numbers of inclusions and completions, adverse reactions and other important information concerning the safety of patients. According to the guidelines on data monitoring committees [26], a Data Monitoring Committee (DMC) might not be implemented in studies with non-critical indications or when the intervention under investigation is characterized and known for not harming patients. EMDR therapy is an evidence-based treatment for PTSD and has been found to be safe in patients with a personality disorder. A (DMC) is therefore not instituted.

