## Method

### Design

The TEMPO study is a single-blind randomized controlled superiority trial with two arms, i.e. EMDR therapy and waiting list. The trajectory of a participant through the study is shown in Fig. 1. The experimental group will receive ten bi-weekly EMDR sessions of 90 min each, with a total duration of 15 h of treatment over 5 weeks. The groups are compared at baseline (pre-randomization; T0), post-intervention (after 5 weeks; T1), 3-month (T3), 6-month (T6) and 12-month (T12) follow-up. At baseline, demographical data will be collected for predictive analyses of treatment success and treatment dropout. At T1, patient dropout will be recorded and a random selection of patients in the experimental condition will be interviewed to assess their experiences with EMDR therapy. Until T3, patients do not receive further treatment, except in a crisis situation. At T3, all patients will be invited by their therapist for a consultation to examine whether (further) treatment is necessary. Any available treatment, except EMDR therapy, will be offered. At T12, when participation is concluded, control patients will also be offered the opportunity to receive EMDR therapy.

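### Adverse events are recorded only when volunteered or observed, while scheduled contacts up to T1 are 11 under EMDR and 1 on the waiting list, so discrete events are ascertained unequally between arms

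*Protocol article*

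**What the plan says.** The Adverse events section states how events come to be recorded: "All adverse events reported spontaneously by the subject or observed by the investigator or his staff will be recorded". Serious events go to the sponsor "without undue delay after obtaining knowledge of the events", so that route also starts with someone learning of the event. Table 1 shows no adverse-event item at any assessment, and none of the described measures is an adverse-event instrument.

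The Design section gives the experimental arm "ten bi-weekly EMDR sessions of 90 min each, with a total duration of 15 h of treatment over 5 weeks". The EMDR therapy section adds a channel that only this arm has: "these consultants review the EMDR sessions through session reports that the therapists share with the consultants directly following each session". Under Waiting list, control patients are told their allocation and next seen for the T1 assessment. The one direct question on side effects is question 5 of the experience interview (Appendix B), which is put to a sample of EMDR patients only.

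For the time after T1, the Design section says "Until T3, patients do not receive further treatment, except in a crisis situation", and then "At T3, all patients will be invited by their therapist for a consultation". After that, both arms may start other treatment.

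The Committees entry says that yearly safety reports go to the ethics committee, and on the data monitoring committee: "A (DMC) is therefore not instituted".

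**The concern.** Under a passive rule, the number of recorded events depends on how often someone is there to hear about or notice one. In this trial that opportunity is tied to allocation. EMDR patients are seen about twice a week by a therapist who writes a report each time. Control patients have no scheduled contact until T1. Participants also know their allocation, which may affect what they volunteer.

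Any event count shown by arm, whether in the final report or in the yearly safety reports, would then mix a true difference with a difference in observation. At equal true rates the expected direction is an apparent excess under EMDR. The reverse error also matters: PD treatment for control patients is postponed until after T3, so events during that wait are a relevant comparator, and they are the ones least likely to be recorded.

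**Working it through.** **Contact counts (from the protocol article)**

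- EMDR sessions: 10 × 90 min = 900 min = 15 h, which agrees with the stated total. Ten sessions in 5 weeks is two a week.
- Allocation to T1: EMDR 10 + 1 = 11; waiting list 1.
- To T3, adding the T3 assessment and the T3 consultation: 11 + 2 = 13 against 1 + 2 = 3.
- To T12, adding the T6 and T12 assessments: 13 + 2 = 15 against 3 + 2 = 5. Treatment started after T3 is not counted and is open to both arms.

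These are maxima for EMDR, because early completers and patients who discontinue attend fewer than ten sessions.

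**Capture model (assumption)**

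The documents give no chance *p* that an event is mentioned or noticed at a contact. I assume the same *p* at every contact, independent contacts, and events spread evenly over the period from allocation to T1. An event arising before the last *k* of the 11 EMDR contacts then has *k* chances to be recorded, with *k* = 1, …, 11 equally likely.

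- Mean probability of being missed by T1 under EMDR: *M* = (1/11) × Σ(1 − *p*)^*k*, summed over *k* = 1 to 11.
- Capture by T1: 1 − *M* under EMDR; *p* on the waiting list.
- Capture by T12 of the same events, with four further contacts in each arm: 1 − *M*(1 − *p*)^4 against 1 − (1 − *p*)^5.

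At *p* = 0.10: Σ0.9^*k* = 0.9 × (1 − 0.9^11)/0.1 = 6.176, so *M* = 6.176/11 = 0.561. Capture by T1 is 0.439 against 0.100. By T12 it is 1 − 0.561 × 0.656 = 0.632 against 1 − 0.590 = 0.410.

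At *p* = 0.20: Σ0.8^*k* = 0.8 × (1 − 0.8^11)/0.2 = 3.656, so *M* = 0.332. Capture by T1 is 0.668 against 0.200.

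| *p* per contact | By T1: EMDR v waiting list | Ratio | By T12: EMDR v waiting list | Ratio |
|---|---|---|---|---|
| 0.05 | 26% v 5% | 5.1 | 39% v 23% | 1.7 |
| 0.10 | 44% v 10% | 4.4 | 63% v 41% | 1.5 |
| 0.20 | 67% v 20% | 3.3 | 86% v 67% | 1.3 |
| 0.30 | 79% v 30% | 2.6 | 95% v 83% | 1.1 |

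The ratio is what recorded counts would show if true rates were equal. It stays above 1 over the whole range and falls as shared contacts accumulate. The T12 columns follow events that arose before T1 and ignore treatment contacts after T3, so they are a rough guide only.

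**Why even spreading matters.** Treating every event as present before the first session would give 1 − 0.9^11 = 69% under EMDR by T1 at *p* = 0.10, and 91% at *p* = 0.20. That overstates capture, because an event in week 4 cannot be noted in weeks 1 to 3.

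**The case against.** The strongest reply is that the article plans no between-arm test of adverse events and names no comparative safety objective. The records serve reporting to the sponsor and the ethics committee. This is correct and limits the point. It does not remove it, because any descriptive count by arm and the yearly safety reports would carry the same imbalance.

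A reader might infer that deterioration on the waiting list goes unseen, or that the trial cannot say which arm fares worse. The documents do not support that. ADP-IV, CAPS-5, SCID-5-P, OQ-45 and the other symptom scales are given to both arms at T1, T3, T6 and T12, with interviewers blind to allocation. The TiC-P asks both arms about care use, and crisis treatment is allowed before T3. What remains exposed is the discrete event between visits that leaves no trace in care use. No passage links these measures to adverse-event recording.

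A reader might also infer that EMDR is bound to show more events. That is only the expectation at equal true rates, since EMDR could lower the true rate. Nor does the rule undermine the decision to have no data monitoring committee: that decision rests on prior evidence about EMDR, not on this trial's counts.

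Finally, the article condenses a fuller protocol, which may hold an event form. But the article does not merely stay silent. It states the recording rule, and the rule is passive.

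**Conclusion.** The point holds for discrete adverse events, chiefly up to T1. The contact counts of 11 against 1 come from the document and need no assumption beyond full attendance. The direction, more events recorded under EMDR at equal true rates, holds at every capture rate tried. The size does not come from the document: about 44% against 10% by T1 at an assumed 10% per contact and 67% against 20% at 20%, given independent contacts, even spreading of events and equal detection at a session and at an assessment. A several-fold gap at T12 cannot be claimed: with the T3 consultation counted and *p* = 0.10 the ratio is about 1.5, before any treatment started after T3. The primary efficacy result is not affected. The change is still worth making, because the remedy is cheap and the control arm's events are those most likely to be missed.

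**What to change.** Add one open adverse-event question, identically worded for both arms, at T1, T3, T6 and T12. Put it in the Data Manager self-report set, so that answers do not reveal allocation to the blinded interviewers. Record the source of each event: asked at a fixed assessment, or noted in a session or otherwise. Base any between-arm summary on the answers from the fixed assessments only, and list session-noted events separately so that none is lost. Serious-event reporting is unchanged.

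With the same scheduled question in both arms, the structural 11-to-1 imbalance drops out of the comparison. Differences in what unblinded patients choose to report may remain.

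The cost is a short amendment, one item at four assessments that already take place, and a few more events to review and process, including someone to read the answers as they arrive. Inclusion started in February 2021, so a question added midway covers only assessments after the amendment. The report should say so.

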### Measurements

There will be five measurement moments, namely at baseline (T0), post-intervention (T1), 3-month follow-up (T3), 6-month follow-up (T6) and 1-year follow-up (T12). While most measures will be conducted at each measurement moment (see Table 1), the Childhood Trauma Questionnaire and the Life Events Checklist will only be administered at baseline and the interview about patients’ experiences with EMDR therapy is exclusively conducted at T1, with only the experimental group. All measurements will take place at the location at which the participant is in treatment or through video calls. The self-report questionnaires will be digitally administered with Data Manager, which automatically invites participants through email on pre-determined dates and then stores the responses safely. Participants will be reminded to fill in the questionnaires, first by mail and second by telephone, to promote complete follow-up data. At baseline, demographical data are collected. Results will be recorded as absolute values.

**Table 1 Tab1:** Schedule of enrolment, interventions and assessments

Timepoint	Study period							
				Post-allocation				
	Enrolment	T0	Allocation	Intervention	T1	T3	T6	T12
**Enrolment:**								
***Eligibility screen***	x							
***Informed consent***	x							
***Allocation***			x					
**Interventions:**								
***EMDR***				x				
***Waiting list***								
**Assessments:**								
***ADP-IV***		x			x	x	x	x
***CAPS-5***^**a**^		x			x	x	x	x
***SCID-5-P***^**a**^	x				x	x	x	x
***TiC-P***		x			x	x	x	x
***EQ-5D-3L***		x			x	x	x	x
***MHQoL***		x			x	x	x	x
***LEC-5***		x						
***PCL-5***		x			x	x	x	x
***CTQ-SF***		x						
***DERS***		x			x	x	x	x
***BSPC***		x			x	x	x	x
***LPFS-BF 2.0***		x			x	x	x	x
***OQ-45***		x			x	x	x	x
***Appendix A/B***^**a**^					x^b^			

*EMDR* Eye Movement Desensitization and Reprocessing, *ADP-IV* Assessment of DSM-4 Personality Disorders, *CAPS-5* Clinician-Administered PTSD scale for DSM-5, *SCID-5-P* Structured Clinical Interview for DSM-5 Personality Disorders, *TiC-P* Treatment Inventory of Costs in Patients with psychiatric disorders, *EQ-5D-3L* EuroQol—5 dimensions—3 levels, *MHQoL* Mental Health Quality of Life, *LEC-5* Life Events Checklist for the DSM-5, *PCL-5* PTSD Checklist for DSM-5, *CTQ-SF* Childhood Trauma Questionnaire—Short form, *DERS* Difficulties in Emotion Regulation Scale, *BSPC* Brief State Paranoia Checklist, *LPFS-BF 2.0* Level of Personality Functioning Scale—Brief Form 2.0, *OQ-45* Outcome Questionnaire-45

^a^Interview

^b^Experimental condition only

